## Methods

### Definition

Several key definitions are outlined below:Efficacy: the efficacy was determined based on the operation duration, operation cost, and hospitalization durationOperation cost: the sum of the operational and material expenses, retrievable from the hospital systemOperation duration: the time from the administration of preoperative anesthesia to the patient's recovery of consciousness in the postoperative periodSafety: the ratio of intraoperative to postoperative complicationsEn bloc resection: complete removal of a lesion without any segmentation or partial lesion remainingR0 resection: the absence of cancerous tissue on the edges of the lesion after resectionPostoperative gastric bleeding: a patient experienced hematemesis, melena, or an unexplained decrease in hemoglobin levels after the operationDelayed perforation: the occurrence of sudden abdominal pain after the operation, accompanied by the detection of retroperitoneal pneumatosis or free gas through imaging examinationPostoperative recurrence: the discovery of a newly investigated tumor-like lesion that is eventually proven to be the same pathology as the previously resected tumorHospitalization duration: the number of days from admission to discharge

### Patient and public involvement

No patients or members of the public were involved in any way in the design of this trial.

### Interventions

The participating operators were required to meet the following criteria:Possess more than 5 years of experience in medicineDemonstrated ability to independently conduct endoscopic operationsOperators with a history of performing no fewer than 300 endoscopic operations annually and a total of at least 1000 procedures

Patients were required to undergo a comprehensive preoperative evaluation to ensure the absence of absolute surgical contraindications. The operation was immediately stopped in the event of an unexpected intraoperative contingency, and appropriate clinical measures were taken accordingly. A detailed analysis and documentation of the possible reasons for such contingencies will be conducted. Intraoperative and postoperative interventions may be adjusted following established guidelines [26]. Implementing ESD or precutting EBLR will not require alteration to usual care pathways (including the use of any medication), and these steps will continue for both trial arms. Regarding postdischarge interventions (regular intake of esomeprazole), we contacted each participant via phone to provide reminders for consistency in medication adherence. This approach was approved by the participants when they signed the informed consent form.

#### ESD

Initially, a high-viscosity solution is employed to elevate the submucosal covering of the tumor. Subsequently, electrocautery knives are used for dissecting the tissue beneath and surrounding the lesion, leaving a resection bed. In the event of a perforation, closure can be facilitated using titanium clips or a purse-string suture [18]. Following the completion of the operation, patients undergo a 48-h observation period during which they fast and regularly take esomeprazole (40 mg, twice daily). Upon discharge, patients are required to continue taking esomeprazole (40 mg, once daily) for 2 weeks.

#### Precutting EBLR

Initially, an electrosurgical snare is positioned on the tumor’s mucosal protuberance, followed by snare resection using an electrosurgical current set at 30 W to precut and remove the covering mucosa. Subsequently, an appropriate ligator is chosen based on the tumor size: a small ligator for tumors within 1 cm, a medium ligator for tumors ranging from 1 to 1.2 cm, and a large ligator for tumors greater than 1.2 cm. After proper ligator installation, the tumor is drawn from the surface and effectively removed using an electrosurgical snare. Closure of the perforation caused by ligation is assisted by employing three-armed clips or titanium clips. Finally, the excised tumor is sent for pathological examination. Postsurgery, fast for 12–24 h is required, followed by a liquid diet for 2–3 days and esomeprazole (40 mg, once daily) for 2 weeks. The steps of the operation and postoperative pathology are shown in Fig. 1*.*

**Fig. 1 Fig1:**
[figure not shown]
Steps of the precutting EBLR and postoperative pathology. **A** The tumor investigated in the fundus of the stomach by white light gastroscopy. **B** The tumor (white arrow) investigated by EUS. **C** The tumor’s covering mucosa was precut and removed. **D** The tumor was drawn from the surface using a transparent ligator. **E** The tumor was removed using an electrosurgical snare. **F** Active perforation was closed with titanium clips. **G** Microscopic view of the tumor. **H** Gastrointestinal stromal tumor was pathologically demonstrated

### Devices

CT, EUS (OLYMPUS EU-M2000, 20 MHz, Japan), and standard endoscopy (AOHUA AQ200L, China) were used for preoperative assessment and follow-up. Standard endoscopes (AOHUA AQ200L, China) and loop snares (MICRO-TECH (NANJING) Co., Ltd., China) were used for mucosal protuberance precutting. Small ligators (TIANJIN TY, Medical Organism Material Research Company Ltd., China) were used for tumors ≤ 10 mm in length; medium ligators (OTSC cap plus ligation band, Ovesco Endoscopy AG, Tubingen, Germany) were used for tumors > 10 mm but ≤12 mm in length; and large ligators (colonoscopy transparent cap plus ligation band, OLYMPUS, Japan) were used for tumors >12 mm in length. All the ligators were disposable. Injectors (OLYMPUS, Japan), an IT knife, a dual knife, and an electronic cutting device (EREB VIO 200S, Germany) were used for ESD.

### Outcomes and follow-up

The primary outcome for the trial was operation duration, and the secondary outcome was operation cost. Both outcomes will be assessed prior to discharge. Additional meaningful indicators, also set as secondary outcomes, include estimated blood loss, intraoperative and postoperative adverse events (such as bleeding, immediate and delayed perforation, infection), tumor recurrence, mortality rates, and hospitalization costs.

The trial’s endpoint will be established as 6 months after the operation of the last included patient. Each patient is given a detailed follow-up evaluation via telephone 6 months after discharge to gather information about their postoperative condition. At the 6-month mark, patients are required to undergo an endoscopic re-examination to assess tumor recurrence.

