We previously introduced a novel endoscopic treatment termed precutting EBL. In this operation, an electrosurgical snare resection is performed to initially remove the mucosa surrounding the tumor, followed by the use of a transparent ligator to suction the tumor. A long-term, single-center study has substantiated its safety and efficacy. Precutting EBL was associated with a significantly shorter operation duration (16.6 min) and lower cost ($603.3 ± 5.9) than ESD ($2783 ± 601), and it was associated with fewer complications [21]. However, precutting EBL has two notable drawbacks. First, pathological specimens were not collected since the tumor spontaneously drops off after ligation, necessitating long-term follow-up for eradication verification. Second, like other ligate-and-let-go techniques, there is a risk of delayed perforation after the operation, which warrants careful consideration [22]. Given that we did not have sufficient samples to assess the possibility of delayed perforation, we opted to perform en bloc resection of lesions after ligation. Although this approach increases the chances of intraoperative perforation, we can promptly address this possibility if it occurs. Consequently, we propose a modified endoscopic operation for small gastric SMT-MPs, termed precutting EBLR. This involves an additional snare resection immediately after ligation. After thorough communication and detailed informed consent, we experimentally performed precutting EBLR on 16 patients. All patients showed rapid postoperative recovery, with no instances of delayed gastric bleeding or perforation. Importantly, subsequent pathological examination confirmed R0 resection in every patient.

To further enhance the clinical validation of precutting EBLR, we opted to initiate a randomized controlled trial comparing the efficacy and safety of ESD and precutting EBLR for the treatment of small gastric SMT-MPs.

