**Assessments:**							
**Baseline characteristics**			X				
**Operation duration**				X			
**Estimated blood loss**				X			
**Intraoperative adverse events**				X			
**Postoperative adverse events**					X	X	X
**Operation cost**				X			
**Hospitalization cost**					X		

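### Postoperative adverse events have no scheduled assessment between discharge and 6 months and no common window from operation, so capture may differ by arm if length of stay differs

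*Protocol article*

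**What the plan says.** **Schedule.** In the Protocol article, the row "Postoperative adverse events" of Table 1 (Participant timeline) is marked at discharge, 6 months and 12 months. Outcomes and follow-up describes the contact behind the 6-month mark: "Each patient is given a detailed follow-up evaluation via telephone 6 months after discharge to gather information about their postoperative condition". That clock starts at discharge, not at operation. At the same time point "patients are required to undergo an endoscopic re-examination to assess tumor recurrence", so the stated purpose of the endoscopy is recurrence. The trial's "endpoint will be established as 6 months after the operation of the last included patient".

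**Early aftercare.** Under ESD, "patients undergo a 48-h observation period during which they fast and regularly take esomeprazole". Under Precutting EBLR: "Postsurgery, fast for 12–24 h is required, followed by a liquid diet for 2–3 days". Neither section says when the patient goes home. The Definition section makes hospitalization duration one of the measures of efficacy.

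**Other contact after discharge.** Interventions says that "we contacted each participant via phone to provide reminders for consistency in medication adherence", without giving the number or dates of these calls. Monitoring provides for monthly audits of each participant's progress and for prompt reporting of adverse events to the trial team.

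**The concern.** The first scheduled look at postoperative events closes at discharge, and the treatment can affect that date. The next is about half a year later, by telephone. If one arm goes home earlier, more of its events move from a period of direct observation to one that relies on later report.

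This matters for three reasons.

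- Late complications are central to the rationale. Of ligation techniques that leave the tumor to drop off, the Background says that "there is a risk of delayed perforation after the operation, which warrants careful consideration", and delayed perforation is a listed safety outcome.
- The trial is open-label, and the abstract says that secondary outcomes are tested for noninferiority. Events missed in the new arm would favor it.
- Postoperative bleeding can be met by an unexplained fall in hemoglobin alone. That needs a blood test, which is far more likely on the ward than in a call months later.

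**Working it through.** The plan gives no figure on this point, so the check is a reading of the schedule followed by an illustration of size.

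**1. Is there a scheduled event assessment soon after discharge?** No. Table 1 has no time point between discharge and 6 months, and the text describes one call. The 12-month mark comes later still and cannot fill an early gap. For patients operated on in the last 6 months of accrual, it also falls after the stated end of the trial.

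**2. Do the other channels fill the gap?** Not as described. The stated purpose of the reminder calls is medication adherence. The audits review progress, with no event questions mentioned. Prompt reporting works only once an event is known. The endoscopy is for recurrence.

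**3. Does discharge differ by arm?** The article leaves this open. ESD has 48 h of observation. For precutting EBLR there are two readings:
- discharge may follow the fast, at 12–24 h, which is shorter than 48 h;
- the liquid-diet days are spent in hospital, giving 12 + 48 = 60 h to 24 + 72 = 96 h, which is longer than 48 h.

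The closing discussion contemplates both equal and shorter stay and names an ambulatory operation as a prospect. The stay may therefore differ, but its direction is not fixed.

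**4. Which events are exposed?** By definition, delayed perforation needs sudden pain plus imaging, so a qualifying case leaves a medical record. Milder bleeding, or bleeding shown only by a laboratory value, is more exposed.

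**5. How large could the effect be?** Let *p* be the true event rate (equal in both arms), *f* the share of events after discharge and *c* the share of those captured at 6 months. In-hospital capture is taken as complete.

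Observed rate = *p* × [1 − *f* × (1 − *c*)]

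False difference = *p* × (1 − *c*) × (*f* in EBLR − *f* in ESD)

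For *p* I use 15.6%, the highest delayed-bleeding figure in the Background. It comes from ESD for early gastric cancer, not from this population. The article gives neither *f* nor *c*, so both are assumed: *f* 50–90% for EBLR and 20–50% for ESD, *c* 50–80%.

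| *f* EBLR | *f* ESD | *c* | Observed EBLR | Observed ESD | False relative reduction | Events per 20 |
|---|---|---|---|---|---|---|
| 50% | 50% | 50% | 11.7% | 11.7% | 0% | 0 |
| 50% | 20% | 80% | 14.0% | 15.0% | 6% | 0.19 |
| 90% | 20% | 80% | 12.8% | 15.0% | 15% | 0.44 |
| 90% | 50% | 50% | 8.6% | 11.7% | 27% | 0.62 |
| 90% | 20% | 50% | 8.6% | 14.0% | 39% | 1.09 |

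The last row is 0.156 × 0.55 = 0.0858 against 0.156 × 0.90 = 0.1404. The ratio is 0.61, and the difference of 0.0546 × 20 is 1.09 events.

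The relative reduction does not depend on *p*, but the event count does. With the same *f* and *c* as the last row, the perforation rates in the Background give 20 × 0.052 × 0.5 × 0.7 = 0.36 events at 5.2% and 20 × 0.012 × 0.5 × 0.7 = 0.08 at 1.2%.

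For scale, 20 patients at 15.6% give 20 × 0.156 = 3.1 expected events per arm.

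**The case against.** The strongest reply is that the harm depends on something the article never states. A reader might infer from the aftercare sections and the ambulatory aim that precutting EBLR patients go home earlier, so that safety is biased in their favor. The article does not support that: no discharge point is given for either arm, equal stay is expressly contemplated, and equal post-discharge shares give no bias. This stands, and it makes the direction conditional.

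A reader might also infer that delayed perforation is the event most likely to be lost, or that delayed bleeding was a reason for changing the technique. Neither follows. Perforation needs imaging and so leaves a record. The Background gives missing pathology and delayed perforation as the two drawbacks; bleeding is only a listed outcome.

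Nor does everything after discharge rest on recall alone. Audits, prompt reporting and records of treated complications will bring some events to light, especially serious ones. The pilot saw no major bleeding and no delayed perforation in 16 patients.

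Finally, this is a condensed article, and a call script may exist in the full protocol. It would therefore be wrong to assert that the calls never ask about events. But Table 1 is a stated schedule, and it anchors the first assessment to discharge and the next to 6 months. That part is not an argument from silence.

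**Conclusion.** The narrow point holds. Postoperative adverse events have no scheduled assessment in the early post-discharge period and no common window counted from operation. Because discharge follows randomisation and may depend on the arm, ascertainment may differ between arms, mainly for milder or laboratory-only events.

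The size is unknown. With equal true rates and the ranges assumed above, the false relative reduction lies between 0% and 39%, at most about one event per 20 patients even at the high 15.6% rate. It is zero if post-discharge shares are equal or if capture at 6 months is complete. A bias towards precutting EBLR requires both that those patients leave earlier and that later capture is incomplete; the article establishes neither.

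This does not touch the primary outcome, operation duration. It is an inexpensive improvement worth making, since with about three expected events per arm at most, one missed event would visibly alter the safety comparison.

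**What to change.** - Count postoperative adverse events over the same fixed window from operation in both arms, for example 30 days, and report that count by arm.
- Add a short scripted event checklist to the post-discharge reminder calls: black stool or vomiting blood, sudden abdominal pain, fever, any hospital visit.
- Hold one such contact on the same postoperative day in both arms. The article gives no dates for the present calls, so the day must be set.
- Add that time point to the adverse-event row of Table 1, and keep the 6-month call for late events.
- In the same edit, reconcile the 12-month mark with the stated end of the trial.

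The cost is a call script, a change to Table 1 and at most one extra short call for each of 40 patients. It alters data collection only and leaves treatment, aftercare and discharge as they are.

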## Data management

### Collection

All the data were collected and verified by two statisticians simultaneously using a spreadsheet (Microsoft Excel 2016) in accordance with each patient’s personal information and medical images. Patients are assigned numerical codes instead of their names to ensure the confidentiality of personal information. To minimize statistical errors, any controversial data is reviewed and discussed by a third person. Preoperative, intraoperative, and postoperative data are collected. Missing data will be declared in the appendix, and the corresponding participant will be considered withdrawn.

Preoperative data included demographic information (age, sex, date of admission) and tumor characteristics (size, layer, location, shape, and density of the echo site investigated via EUS). Intraoperative data included the operation date, duration, estimated blood loss, and details related to intraoperative perforation (size, duration, and amount of titanium clips). Postoperative data included the size of the resected tumor (assessed by ruler), tumor pathology (tumor type, mitotic count, achievement of R0 resection or not, and immunohistochemistry), postoperative management (duration of fasting and liquid diet, use of medications), postoperative symptoms and adverse events, hospitalization duration and cost, operation cost, and 6-month follow-up outcome.

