## Introduction

### Background and rationale

Submucosal tumors (SMTs) histologically include both epithelial and nonepithelial tumors. Nonepithelial tumors typically present as protruding lesions or masses covered with intact mucosa [1]. Large SMTs (≥2 cm) in the stomach may lead to early-stage complications such as bleeding or perforation, resulting in symptoms such as abdominal bloating, pain, hematemesis, or melena, which prompt patients to seek medical attention. In contrast, small gastric SMTs (<2 cm) are typically discovered incidentally during endoscopy without any apparent symptoms [2, 3].

The risk of small gastric SMT-MPs has been underestimated [4]. Studies suggest that 60–70% of SMT-MPs are pathologically identified as gastrointestinal stromal tumors (GISTs) and categorized as potential malignancies regardless of their size [2, 3]. However, although surgeons propose resection for large gastric SMT-MPs, clinical controversy persists [1, 5, 6]. In a retrospective study conducted by Ge QC et al. [7], a cutoff value of 1.48 cm was established to predict the malignant potential of GISTs. Tumors larger than 1.48 cm were associated with greater malignant potential, warranting intensive surveillance or endoscopic surgery. According to the modified National Institute of Health, the risk of small GISTs varies only with the mitotic count. The classifications included very-low risk (mitotic count ≤5), intermediate risk (mitotic count between 5 and 10), and high risk (mitotic count >10). Some advocate for imaging surveillance as the primary approach, suggesting resection only when tumor progression is confirmed. This includes cases where the tumor shows signs of increasing size, irregular borders, or pathological confirmation as a cancer [8]. Although endoscopic ultrasound (EUS) is a common method for diagnosing gastrointestinal superficial lesions, its role in diagnosing SMT-MPs has not been determined. Additionally, consistent observation of dynamic changes in tumor size and border length for patients with SMT-MPs < 16 mm is challenging. Although EUS-guided fine needle aspiration (EUS-FNA) is often employed for pathology, it may not fully reveal the pathological features of GISTs due to heterogeneity. In conclusion, en bloc resection is crucial for both diagnosis and prognosis [9].

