Endoscopic resection, in comparison to open or laparoscopic surgery, yields a shorter operation duration, reduced blood loss, and shorter average hospitalization duration [9–14]. Endoscopic submucosal resection (ESD) has been demonstrated to be feasible for treating gastric SMTs. Guidelines from the European Society of Gastrointestinal Endoscopy (ESGE) and the American Society for Gastrointestinal Endoscopy (ASGE) recommend ESD as the preferred treatment for most gastric superficial neoplastic lesions [15, 16]. However, its effectiveness is limited for lesions originating from deeper layers such as the muscularis propria, increasing the complexity of the operation and the risk of complications. A systematic review by Ichiro Oda et al., encompassing more than 300 patients with early gastric cancer treated with ESD, identified several complications associated with the procedure. These complications included perforation (1.2–5.2%), bleeding (7% for immediate bleeding, up to 15.6% for delayed bleeding), stenosis (0.7–1.9%), aspiration pneumonia (0.8–1.6%), and air embolism, among others [17]. Although management strategies exist for these adverse events, they demand a higher level of technical expertise, adding to the financial burden and psychological stress on patients. Furthermore, ESD may not always achieve R0 resection, posing challenges for diagnosis and prognosis [18, 19]. According to an analysis of 733 patients with upper gastrointestinal SMT-MPs, extensive tumor connection was identified as a risk factor for incomplete resection [20]. In a multicenter prospective study by Ye LP et al. involving 692 patients, the R0 resection rate was 84.2% [19]. Hence, a more judicious treatment approach is imperative.

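### R0 is defined by the absence of cancerous tissue at the edge, so a benign leiomyoma cannot fail it as written and the recorded R0 rate can be inflated

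*Protocol article*

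**What the plan says.** The Definition section of the protocol article defines R0 by one condition: no cancerous tissue at the edges of the resected lesion. The Recruitment section admits muscularis propria tumors below 1.6 cm on endoscopic ultrasound and sets no histological criterion. The Collection section lists "tumor pathology (tumor type, mitotic count, achievement of R0 resection or not, and immunohistochemistry" among the postoperative data and does not limit R0 to any tumor type.

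The Background and rationale section reports that "60–70% of SMT-MPs are pathologically identified as gastrointestinal stromal tumors (GISTs) and categorized as potential malignancies regardless of their size". For the 16 pilot patients it says that "subsequent pathological examination confirmed R0 resection in every patient". Table 2 shows 11 GISTs, 5 leiomyomas and R0 in 16 (100%). The same Background section notes that ESD does not always reach R0 and cites a study of 692 patients in which "the R0 resection rate was 84.2" percent.

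R0 is not among the outcomes. The primary outcome is operation duration. Operation cost is secondary, and the further items named as secondary "include estimated blood loss, intraoperative and postoperative adverse events (such as bleeding, immediate and delayed perforation, infection), tumor recurrence, mortality rates, and hospitalization costs".

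**The concern.** The definition does not fit the population. A leiomyoma is benign and contains no cancerous tissue, so it meets the condition whatever its margin looks like. Followed as written, a leiomyoma with tumor at the cut edge is coded R0, and the incomplete resection does not show in that field.

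This matters for three reasons. R0 is the only microscopic margin result that the Collection section lists. The Background uses R0 in arguing for the new technique: it faults ESD for not always achieving R0 and stresses the pilot's complete record. The limitations paragraph of the Discussion concedes that six months may be too short to observe recurrence, so margin status is the main early evidence of complete removal. A published R0 rate that up to about a third of patients cannot fail would be hard to interpret beside the cited 84.2%.

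**Working it through.** **Inputs.** Pilot: 11 GIST, 5 leiomyoma, R0 in 16 of 16 (Table 2). GIST share of these tumors: 60–70%, so 30–40% are not GIST (Background). Cited R0 rate: 84.2% (Background). Planned arm size: 20 (Allocation).

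**Step 1: reproduce the plan's figures.** 11 + 5 = 16; 11/16 = 68.75%; 5/16 = 31.25%; 16/16 = 100%. These agree with Table 2.

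**Step 2: what the pilot shows under the literal reading.** Only the 11 GISTs could have failed. With no failures in n tumors, the exact two-sided 95% lower limit is 0.025^(1/n).
- All tumors: 0.025^(1/16) = 79.4%.
- GIST only: 0.025^(1/11) = 71.5%.

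The point estimate is 100% both ways; the lower limit falls by 79.4 − 71.5 = 7.9 points. If the leiomyomas passed only by definition, the true proportion with tumor-free margins lies somewhere between 11/16 = 68.75% (all five involved) and 16/16 = 100% (none involved). The documents do not say where.

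**Step 3: what the trial would record.** Let f be the share of benign tumors, which pass automatically, and p the true tumor-free margin rate, assumed equal in both tumor types.
- Recorded R0 = f + (1 − f)p.
- Inflation = f + (1 − f)p − p = f(1 − p).

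The table assumes that all non-GIST tumors are benign. The values of p are also assumptions, because the protocol gives no expected margin rate for the trial.

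| p | Inflation, f = 30% | Inflation, f = 40% |
|---|---|---|
| 100% | 0 | 0 |
| 90% | 3.0 points | 4.0 points |
| 84.2% | 4.7 points | 6.3 points |
| 80% | 6.0 points | 8.0 points |

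At the pilot mix, f = 31.25% and p = 84.2%, recorded R0 is 0.3125 + 0.6875 × 0.842 = 89.1%. The recorded non-R0 rate is then 0.6875 × 15.8% = 10.9%.

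**Step 4: effect on a comparison of arms.** If both arms have the same tumor mix, the f term cancels and a true difference d in margin rates is recorded as (1 − f)d. At f = 31.25%, a difference of 15.8 points would be recorded as 10.9. The definition shrinks a difference and does not favour one arm.

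**The case against.** The strongest reply is that cancerous is loose wording for lesion tissue. The pilot reports R0 for all 16 tumors, which fits a pathologist who read every margin for tumor of any kind. The literal reading is not clear-cut for GIST either, since the Background calls these tumors only potential malignancies. Counting exactly 11 informative tumors is therefore one interpretation. This stands: the documents do not show how the margins were judged. But a definition that leaves this open for both main tumor types needs correcting.

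A reader might infer that recorded R0 rates are in fact inflated, or that the pilot's 100% is overstated. The documents support neither. No involved leiomyoma margin is reported, inflation is zero if those margins were clear, and the pilot estimate is 100% with or without the leiomyomas. The pilot also reports en bloc resection in 16 of 16. That measure does not depend on histology, although it is not a microscopic margin.

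A reader might also infer that the randomized comparison is compromised. R0 is not a primary or secondary outcome, is not part of the efficacy or safety definition, and plays no role in the sample size. Recurrence, which is listed, is defined by matching pathology and so covers benign tumors too.

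The 84.2% serves only as an illustration. The cited study's R0 definition and tumor mix are not given, and if it used similar wording its figure is already a recorded rate. In an arm of 20, the step from 15.8% to 10.9% non-R0 is 20 × 0.158 = 3.2 against 20 × 0.109 = 2.2 patients, about one patient.

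**Conclusion.** The concern holds as a defect of definition. Followed as written, the rule codes every benign leiomyoma as R0, so the field carries no margin information for those tumors: about 31% on the pilot mix, or 30–40% if all non-GIST tumors are benign. The recorded rate can be too high by f(1 − p), from zero when benign margins are clear to 6–8 points at an assumed p of 80%. This assumes the literal reading and equal margin involvement in both tumor types. On the same reading the pilot supports a lower limit of 71.5% instead of 79.4%, with the estimate unchanged. Actual inflation is not shown. The primary conclusion and the sample size are not affected. The correction is still worth making, because R0 is the only microscopic margin result collected and the article's rationale leans on it.

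**What to change.** In the Definition section, replace cancerous tissue with tumor tissue of the resected lesion, of any histological type, at the microscopic margin. Apply this to all patients in both arms, including those already treated. Report R0 overall and by tumor type; both items are already collected, so no new variable is needed. State whether the pilot's 16 of 16 was judged by that definition, and if not, restate it by tumor type.

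The cost is one changed phrase and, where existing reports leave benign margins undescribed, a second look at specimens that already go to pathology. The small downside is that the R0 rate may look slightly less favourable.
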